**Discussion:**

If the system is effective in reducing depressive and/or manic symptoms (and other symptoms of bipolar disorder) and the rate of episodes, there will be basis for extending the use to the treatment of bipolar disorder in general and in larger scale.

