### Outcomes

#### Primary outcomes

Differences in clinically rated depressive and manic symptoms measured using HDRS-17 and YMRS, respectively, between the intervention group and the control group.Differences in depressive and manic symptoms measured using HDRS-17 and YMRS, respectively, between the intervention group and the control group in patients with presence of depressive and manic symptoms (defined as HDRS-17 > 0 or YMRS > 0) *at any given visit* with the researcher during the 9-month trial period.Differences in depressive and manic episodes defined as HDRS-17 ≥14 or YMRS ≥14 between the intervention group and the control group.

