### Statistical power and sample size calculation

The statistical power and sample size was calculated using http://stat.ubc.ca/~rollin/stats/ssize/n2.html.

The primary outcomes are a) differences in the level of depressive and manic symptoms based on HDRS-17 and YMRS, respectively and b) differences in the number of depressive and manic episodes defined as HDRS ≥14 and YMRS ≥14, respectively.The clinical relevant difference in the level of depressive and manic symptoms is defined as a minimum of three scores on HDRS-17 and YMRS, respectively, and the standard deviation (SD) is set to 7 with a mean score of 7 vs. 10 in the intervention group and the control group, respectively. The statistical power to detect a three score difference in the areas under the curves between the intervention group and the control group on HDRS-17 and YMRS, respectively, is 80% with α = 0.05 for a two-sample comparison of means including a minimum of 86 patients in each of the two sub-groups in the intervention group (smartphones capable of collecting automatically generated behavioural data or not) (n = 172) and 86 patients in the control group (n = 86). This results in an estimated total sample size of 258 patients.The clinical relevant difference in the number of depressive and manic episodes is defined as a minimum of 10% difference and the SD is set to 23% with a mean score of 40% vs. 50% in the intervention group and the control group, respectively. The statistical power to detect a 10% difference in the area under the curves between the intervention group and the control group on the number of depressive and manic episodes is 80% with α = 0.05 for a two-sample comparison of means including about the same number of patients in each of the two sub-groups in the intervention group (smartphones capable of collecting automatically generated behavioural data or not) (n = 172) and in the control group (n = 86).

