### Statistical methods

Data from all randomized patients are collected until dropout or the end of the trial period. Analysis will be carried out with an intention-to-treat (ITT) approach. The primary outcomes are differences in depressive and manic symptoms using HDRS-17 and YMRS, respectively, during the 9-month trial period. Analysis will be done employing a linear mixed effects model with random intercept for each participant and a fixed effect of visit number. Differences in outcomes between the intervention group and the control group will be analyzed, firstly in an unadjusted model (except for potential differences in baseline values of the outcome variable) and then in models adjusted for age and sex as possible prognostic variables.

Furthermore, analysis will be done employing a linear mixed effects model with random intercept for each participant and a fixed effect of visit on differences in HDRS-17 and YMRS in patients with presence of depressive and manic symptoms (defined as HDRS-17 > 0 or YMRS > 0) at a given time point during the trial period between the intervention group and the control group. Additionally, analysis of the primary outcomes of differences in depressive and manic episodes defined as HDRS ≥14 and YMRS ≥14 during the trial period will be done employing survival analysis with reasons for censoring being date of death or date of drop out.

Potential interactions between randomization group (intervention group or control group) and visit number in the analyses will be investigated and reported accordingly. The statistical threshold for significance is p ≤ 0.05 (two-tailed). Data will be managed by [name] and entered using Epidata® (Epidata Association, Odense, Denmark). All analyses will be done using STATA version 12 (StataCorp LP, College Station, TX, USA).

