### Perspectives

Electronic monitoring using smartphones represents a flexible and adjustable system that could be of great support for both patients and health care providers, and possibly increase the patients’ illness insight, empowerment and awareness of early warning signs of upcoming depressive or manic episodes.

If the Monsenso system is proved effective in reducing the level of depressive and/or manic symptoms (and other symptoms of bipolar disorder) and the rate of depressive and manic episodes in the present trial, there will be basis for extending the use of the system to the treatment of patients with bipolar disorder in general and in a larger scale. Potentially electronic monitoring using smartphones may be applied in relation to patients suffering from other mental disorders. In this way, it is possible that outpatient treatment in general can be optimized, and that the frequency of necessary health care provider/physician/clinician and other clinical staff visits can be reduced and be more flexible according to the needs of the patients.

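### Up to six overlapping primary comparisons are each judged at p ≤ 0.05 with no hierarchy, alpha split or success rule; if any one suffices, the familywise error is roughly 14–25%

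*Protocol article*

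**What the plan says.** The Primary outcomes section of the protocol article gives three entries, each covering depression and mania:

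- "Differences in clinically rated depressive and manic symptoms measured using HDRS-17 and YMRS, respectively, between the intervention group and the control group";
- the same two scales "in patients with presence of depressive and manic symptoms (defined as HDRS-17 > 0 or YMRS > 0");
- "Differences in depressive and manic episodes defined as HDRS-17 ≥14 or YMRS ≥14 between the intervention group and the control group".

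Read by scale, that is up to six comparisons. It is five if the *or* in the last entry makes episodes a composite.

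Other sections count differently. The sample size section opens with "The primary outcomes are a) differences in the level of depressive and manic symptoms based on HDRS-17 and YMRS, respectively and b") the number of episodes. That is two outcome types on two scales, or four comparisons, without the symptomatic subset. Statistical methods first names only HDRS-17 and YMRS, then refers to "analysis of the primary outcomes of differences in depressive and manic episodes defined as HDRS ≥14 and YMRS ≥14 during the trial period".

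The decision criterion is a single line in Statistical methods: "The statistical threshold for significance is p ≤ 0.05 (two-tailed"). The sample size calculation also uses α = 0.05 for each scale. The symptom scores are fitted first with baseline adjustment only and then with age and sex added. Neither model is named as decisive.

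**The concern.** The article itself fixes the primary list, the threshold and the models. It does not say which result, or which combination of results, decides whether the system works. With several primary tests each at 0.05, an ineffective system has a well above 5% chance of producing at least one significant primary result.

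A split result is realistic here. According to the Background, the preceding trial found no overall difference, while its sub-analyses pointed to more sustained depressive symptoms and fewer manic symptoms. If this trial gives a similar pattern, the plan offers no agreed way to read it, and the choice of which primary outcome to stress would be made after the results are known.

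**Working it through.** **The plan's own figure.** Inputs from the sample size section: difference 3, SD 7, α = 0.05 two-sided, power 80%.

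n per group = 2 × (1.960 + 0.842)² × 7² / 3² = 85.5, so 86. The stated figure is reproduced. The calculation is for one scale at full α.

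**Independence ceiling**, 1 − 0.95^k:

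- k = 2: 9.75%
- k = 4: 18.5%
- k = 6: 26.5%

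**Allowing for correlation.** The tests are not independent, because the subset and episode outcomes come from the same HDRS-17 and YMRS scores. The document gives no correlations, so these are assumptions: 0.3 to 0.95 between tests on the same scale, and 0 to 0.4 between scales. The first four rows below are multivariate normal simulations (1,000,000 draws).

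The last row is a patient-level simulation under no effect. It used 86 vs 172 patients, four post-baseline visits and skewed scores. Patient means stood in for the mixed model, with a log-rank test on the first score ≥14. There were 4,000 trials per setting, so the Monte Carlo standard error is about √(0.16 × 0.84 / 4000) = 0.6 percentage points.

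| Same-scale correlation | At least one of six, either direction | Benefit only | A symptom test and an episode test both significant |
|---|---|---|---|
| low | 23.6–24.6% | 12.0–12.8% | 2.2–2.4% |
| 0.5–0.7 | 21.5–22.5% | 10.9–11.6% | 3.1–3.3% |
| 0.6–0.9 | 19.0–19.8% | 9.5–10.2% | 3.4–3.5% |
| 0.7–0.95 | 17.3–18.1% | 8.7–9.3% | 4.0–4.2% |
| patient-level | 14.3–16.4% | 7.3–9.3% | 3.9–4.6% |

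In the patient-level runs the subset test nearly repeats the full test (correlation 0.92–1.00), and the episode test correlates at about 0.75 with it. That is why those values are lowest.

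For smaller families, under the same assumed normal correlations:

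- four comparisons (both scales in all patients, plus episodes): 15.3–18.0%;
- HDRS-17 and YMRS in all patients only: 9.3–9.8%.

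**Power if α is split over two scales.** Power = Φ(3/SE − z), with z = 1.960 at α = 0.05 and 2.241 at α = 0.025.

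- 172 vs 86: SE = 7 × √(1/172 + 1/86) = 0.9245 and 3/SE = 3.245. Power is Φ(1.285) = 90% at 0.05 and Φ(1.004) = 84% at 0.025.
- 86 vs 86: SE = 7 × √(2/86) = 1.0675 and 3/SE = 2.810. Power is Φ(0.850) = 80% at 0.05 and Φ(0.569) = 72% at 0.025.
- Bonferroni over all six (α = 0.0083): 73% for 172 vs 86 and 57% for 86 vs 86.

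**The case against.** **The wording of the conclusion.** A reader might infer that the protocol lets improvement on one scale suffice, from "If the system is effective in reducing depressive and/or manic symptoms" in the Abstract's Discussion and "proved effective in reducing the level of depressive and/or manic symptoms" in Perspectives. The documents do not support that. Both sentences go on to join the episode rate with *and*, so the *and/or* covers symptoms only. Taken literally as a rule (a symptom result and an episode result), they would hold the two-sided error at about 2–5%, as the last column of the table shows. This objection stands against the one-scale reading. It does not rescue the plan, because these sentences are discussion prose about wider use. Nothing under Primary outcomes, the sample size section or Statistical methods makes a claim depend on both.

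**The size.** A reader might take 26.5% as the risk. That needs independent tests, which outcomes cut from the same two scales cannot be. It also counts significant harm, which would not support adoption. And the document states no familywise target; 5% is its per-test threshold. All of this stands, and it is why a range and a benefit-only figure are given.

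**The count.** Six is the maximum under one section, and the sample size section supports four. This stands too, but the inconsistency is part of the problem.

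**An analysis plan may settle it.** Multiplicity detail is often left there. Here, however, the article itself fixes the threshold and the primary labels, so a later plan would have to change what is written, not merely add to it.

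**The models.** Statistical methods does give an order of fitting, and the error figures above do not include the second model. The multiple models are a lesser point.

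**Conclusion.** The point holds in this form: up to six overlapping comparisons are labelled primary, the count differs between sections, and all are judged at two-sided 0.05 with no rule for combining them.

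If any one significant result counts as success, the familywise error is roughly 14–25%. The lower part of that range is more plausible, given how closely the subset and episode tests follow the full-sample tests. Restricted to false findings of benefit it is about 7–13%, against 2.5% for a single test. Even the narrowest reading, HDRS-17 and YMRS in all patients, gives 9–10%.

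The six-test ranges rest on assumed correlations and on the any-one-suffices reading, which the document neither states nor excludes. Under a symptom-and-episode rule the error would be near or below 5%, but no such rule is stated.

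**What to change.** Before any analysis, and as a documented amendment:

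- Make HDRS-17 and YMRS in all randomised patients, intervention versus control, the decisive pair. Test them with Holm at overall two-sided 0.05.
- Name one of the models already described as decisive, and report the other as supportive.
- Place the symptomatic-subset and episode analyses below the pair, either as secondary or later in a fixed sequence that opens only once both scales are significant.
- State that the efficacy claim rests on the Holm-adjusted result, and use the same primary list in every section.

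The cost in power is modest for the whole-arm comparison: 90% to 84% at the strictest Holm step, before attrition. It is not free for a single phone sub-group (80% to 72%), so sub-group comparisons should not be claimed at 80%. Correcting over all six instead would leave 73% for the whole-arm comparison, so shortening the decisive list is the better route.

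This changes the primary outcomes and is more than wording. The article says that outcomes have not changed since the trial began, so the amendment must be dated and reported. With recruitment ongoing and the analysts kept blinded, it is still credible now. If the sponsor wants to keep all the listed outcomes primary, the minimum is to write down an explicit success rule or hierarchy for them.

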### Ethical considerations and approval

Ethical permission for the MONARCA II trial has been obtained from the Regional Ethics Committee in The Capital Region of Denmark and The Danish Data Protection Agency (H-2-2014-059). The law on handling of personal data will be respected. The patients’ journals will only be read to confirm information regarding the patients’ clinical history. The trial was registered at ClinicalTrials.gov as NCT02221336 on the 26^th^ of September 2014. Link to the trial registration: https://clinicaltrials.gov/ct2/show/NCT02221336?term=MONARCA+II&rank=1. All positive, neutral and negative findings of the trial will be published according to the CONSORT guidelines [32]. All electronic monitored data are stored at a secure server at Capital Region, Copenhagen, Denmark. The usual health care provider/physician/clinician of the patients randomized to the intervention group are contacted by letter at the beginning of the trial and informed about the trial and that they might get contacted by the MONARCA II study nurse if there are signs of deterioration of the patient.

All potential participants are invited to receive information about the MONARCA II trial on an individual basis where the information is given in a quiet and undisturbed office. All information is presented in both written and verbal form and participants can bring a friend or relative to the introduction conversation. Participants are informed that participation is voluntary and that consent can be withdrawn at any time during the trial without this having any consequences for current and future treatment options. All participating patients sign a consent form and get a copy of this and their rights as a participant in a clinical trial. All participating patients are offered to loan a smartphone free of charge during the trial period, and economic costs due to data traffic from the Monsenso system are refunded. Participants do not receive any economic compensation for participating in the MONARCA II trial.

## Results

Recruitment is ongoing.

## Discussion

There are yet few studies on electronic self-monitoring in bipolar disorder, and the evidence of electronic self-monitoring has been sparingly investigated and is limited by methodological issues and by a lack of RCTs [51]. Although the idea of electronic self-monitoring seems appealing, studies using rigorous methodology investigating beneficial and possible harmful effects of electronic self-monitoring are needed.

Our group, consisting of psychiatrists, bipolar disorder researchers and IT experts, developed the MONARCA system in close collaboration with patients with bipolar disorder [25,26]. The MONARCA system included a feedback loop on subjective self-monitored measures between patients and clinicians and was tested by the authors in multiple studies, this including a RCT [20,27,28,31]. Subsequently a new version, the Monsenso system, was developed. The MONARCA II trial is the first trial investigating the effect of electronic self-monitoring of subjective measures including a feedback loop integrating subjective as well as automatically generated behavioural data on measures of illness activity on depressive and manic symptoms in patients with bipolar disorder.

### Limitations

#### The intervention

The MONARCA II trial is designed to investigate the effect of the total Monsenso system, comprising daily self-monitoring of subjective measures and an integrated feedback loop (based on either subjective self-monitored measures or a combination of subjective self-monitored measures and automatically generated data on measures of illness activity) between patients and health care providers, compared with using a smartphone for normal communicative purposes. Thus, it will not be possible to address the effect of the individual elements of the intervention.

The integrated feedback loop is based on prediction models based on self-monitored subjective self-monitored measures and for those smartphones capable of collecting these data also on automatically generated behavioural data on measures of illness activity. The integrated feedback loop and prediction models in the Monsenso system are therefore not based on the same amount of data in the two smartphone groups. The prediction models in the integrated feedback loop are adjusted during the trial period (a learning model), due to increasing technical possibilities, to achieve the best prediction possible.

#### The control group

As in any other non-pharmacological treatment trial is it always a challenge to define a proper control group. The MONARCA II trial is designed to include a control group of patients using a smartphone for normal communicative purposes, a placebo smartphone. Automatically generated behavioural data on measures of illness activity is collected on all patients using a smartphones capable of collecting these data during the trial period, including the patients in the control group, this allowing for correlation analyses between depressive and manic symptoms and the automatically generated behavioural data on measures of illness activity in a larger sample of patients with bipolar disorder.

### Generalizability

A RCT represents a study design with possible high interval validity, but this with a possible cost of lower external validity and thereby lower generalizability of the study results. The MONARCA II trial recruits patients who have received treatment at and been discharged from a tertiary specialized mood disorder clinic, however including patients with recent onset of bipolar disorder, whom in most countries are treated elsewhere. Further, the trial has a pragmatic design with few exclusion criteria. In addition, as the Monsenso system is user-friendly for both the patients and the health care providers, and previous MONARCA studies showed a high acceptance and compliance of the previous system [25–28], the findings of the MONARCA II trial are believed to be generalizable to patients with bipolar disorder in general.

### Perspectives

Electronic monitoring using smartphones represents a flexible and adjustable system that could be of great support for both patients and health care providers, and possibly increase the patients’ illness insight, empowerment and awareness of early warning signs of upcoming depressive or manic episodes.

If the Monsenso system is proved effective in reducing the level of depressive and/or manic symptoms (and other symptoms of bipolar disorder) and the rate of depressive and manic episodes in the present trial, there will be basis for extending the use of the system to the treatment of patients with bipolar disorder in general and in a larger scale. Potentially electronic monitoring using smartphones may be applied in relation to patients suffering from other mental disorders. In this way, it is possible that outpatient treatment in general can be optimized, and that the frequency of necessary health care provider/physician/clinician and other clinical staff visits can be reduced and be more flexible according to the needs of the patients.
